### Data and Safety Monitoring

Careful evaluation to ascertain the toxicity and clinical response will be performed. The principal investigator will monitor the data and toxicities in order to identify trends quarterly. The principal investigator will be responsible for revising the protocol as needed to maintain safety. The NCI IRB will review submitted adverse events monthly to evaluate trends and will require a follow-up plan from the principal investigator whenever a trend is identified.

The study will be monitored by the NCI/CCR Data Safety and Monitoring Board (DSMB) on an annual basis to evaluate the safety of the two arms. The serious adverse events (typically grade 3 or greater toxicities) will be reported according to type of toxicity, maximal grade noted per patient, and for toxicities with at least a possible attribution to the therapy provided on that arm. Comparisons will be made between the two arms using Cochran-Armitage tests for trend, or other appropriate methods, to determine if there is increased toxicity associated with either arm.

Beginning at the first annual DSMB meeting after 35 patients have been randomized, annual interim evaluations will be performed to determine if there is sufficient evidence to terminate accrual because of a better than expected improvement in survival.

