### Stratification and Randomization

Registration of patients onto this study will take place within 24 hours of the patient signing the consent by faxing a completed eligibility checklist to the Central Registration Office. This trial will consist of three stages: Lead-in Stage includes the time period from 3 months to 14 months following resection. Patients who present for evaluation prior to month 11 post resection will be enrolled in this stage prior to randomization. Stage 1 includes MSLS with HIPEC and CRS and the recovery period. Patients who are randomized to receive surgical intervention will be entered on stage 1. Stage 2 is the follow up period. Patients who are randomized to surveillance will be directly entered on stage 2; patients who are randomized to the MSLS arm will be entered on stage 2 upon recovery from the operative procedure. After 11-14 months following primary resection, the patients will be stratified and randomized by the Central Registration Office to undergo MSLS with HIPEC and CRS or standard-of-care surveillance (SC) without surgery. The Central Registration Office will notify the study coordinator of the results of randomization. Patients must be randomized within 2 weeks of the baseline imaging studies. Patients who are randomized to the MSLS arm must be treated within 2 weeks of randomization.

Patients will be stratified according to two factors: 1: Presenting with PC, which was completely resected, and/or ovarian metastases (incidence of recurrent PC > 60%) vs. presenting with tumor perforation, T4 lesions that required adjacent organ resection, and/or emergency presentation with bleeding or obstructing lesions (incidence of recurrent PC < 40%), and 2: Receiving adjuvant chemotherapy for less than 6 months vs. > 6 months. This will generate 4 strata.

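### The between-arm toxicity comparison appears to rest on events attributed to each arm's own therapy, so it is not like-for-like and tends to overstate excess toxicity in the second-look arm

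*Protocol article*

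**What the plan says.** The protocol article, Data and Safety Monitoring, sets out what the monitoring board receives each year: "The serious adverse events (typically grade 3 or greater toxicities) will be reported according to type of toxicity, maximal grade noted per patient", and, as a third element of the same sentence, "for toxicities with at least a possible attribution to the therapy provided on that arm".

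The next sentence gives the test, "Comparisons will be made between the two arms using Cochran-Armitage tests for trend, or other appropriate methods", and its purpose, "to determine if there is increased toxicity associated with either arm". It names no separate event set and no significance level.

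On what each arm receives:
- Under Stratification and Randomization, MSLS patients must be treated no later than two weeks after randomization. The alternative is "standard-of-care surveillance (SC) without surgery", and those patients enter follow-up directly.
- Under Standard of Care Surveillance (SC) Arm, follow-up is the same in both arms, and SC patients with peritoneal recurrence are offered exploration with possible cytoreductive surgery (CRS) and heated intraperitoneal chemotherapy (HIPEC).
- Under Post-randomization surveillance for both arms, patients on either arm who develop metastases are offered surgery and/or referral for systemic therapy.

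**The concern.** The question is two-directional and comparative: does either arm carry more toxicity? The event set described just before it is defined separately within each arm. In MSLS, an event counts if it might be due to an operation that every patient has almost at once. In SC, it counts only if it might be due to whatever therapy that patient has received by then, which at first is none. The shared follow-up schedule supplies no balancing therapy.

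The same clinical event, bowel obstruction for example, can be counted in MSLS as possibly surgical and left out in SC as due to disease. The person judging attribution will know whether the patient was operated on. It is also not defined whether salvage treatment after recurrence in SC is therapy provided on that arm.

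At stake is the board's view of net serious morbidity. The trial asks whether an invasive operation is justified in patients with no evidence of disease. A comparison tilted by its own event definition could suggest an MSLS excess that all-cause data would not show, while missing non-fatal complications of late-detected disease in SC.

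**Working it through.** **The plan's own figures.** The safety comparison has no stated figure. The only design calculation concerns survival, and it reproduces: 4 × (1.2816 + 0.8416)² / (ln 1.991)² = 38.02 deaths for 80% power at one-sided 0.10, against 38 stated. The present point does not touch it.

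**Inputs for the illustration**
- From the document (Statistics): n = 35 per arm.
- Assumed, because the document gives none: true all-cause grade 3+ rate p = 0.30 in both arms; 80% of MSLS events attributed; a share f of SC events attributed; two-sided level 0.05.
- Test: with a yes/no outcome the Cochran-Armitage test is the pooled z test, z = (p₁ − p₂) / √[p̄(1 − p̄) × 2/35]. Rejection probabilities come from exact enumeration of two binomials.

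**Filtered rates.** MSLS: 0.30 × 0.80 = 0.24, or 8.4 of 35 patients expected. SC: 0.30 × f.

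| SC events attributed (f) | SC filtered rate | Expected SC patients | Rejection at p = 0.30 | Range for p = 0.20 to 0.50 |
|---|---|---|---|---|
| 0% | 0 | 0 | 98% | 83–100% |
| 10% | 0.03 | 1.05 | 81% | 61–97% |
| 25% | 0.075 | 2.6 | 50% | 35–76% |
| 50% | 0.15 | 5.25 | 15% | 12–27% |
| 80% | 0.24 | 8.4 | 4.8% | about 5% |
| no filter (0.30 vs 0.30) | 0.30 | 10.5 | 5.1% | 4.3–5.1% |

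Worked line for f = 25%: p̄ = (0.24 + 0.075)/2 = 0.1575; standard error = √(0.1575 × 0.8425 × 2/35) = 0.0871; z at the expected rates = 0.165/0.0871 = 1.89, close to the 1.96 cut-off, hence rejection near one half.

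True all-cause toxicity is equal in every row. The error rate returns to about 5% only when the attributed shares match.

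**Can f be above zero?** Yes. The Abstract expects about 55% of such patients to develop peritoneal carcinomatosis: 0.55 × 35 = 19.25. If 25% to 75% of these were explored (assumed), 4.8 to 14.4, or about 5 to 14 SC patients, would have major treatment to which toxicity could be attributed. That happens only after recurrence, so f is likely to be lowest at the early annual reviews.

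**Sensitivity to single counts (two-sided Fisher).** 6 vs 0: 2 × C(35,6)/C(70,6) = 2 × 1,623,160/131,115,985 = 0.025. 5 vs 0: 0.054. 6 vs 1: 0.106. One attributed SC event can change the conclusion.

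**The case against.** The attribution phrase belongs to the reporting sentence and can be read as one of three ways of tabulating events. The test sentence does not say that it is limited to attributed events, and it allows other methods. This is fair: the restriction of the test is an inference. It is still the natural reading, since no other event set is offered.

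A reader might go further and infer that the SC rate is zero by construction, so that a significant difference is guaranteed. The documents do not support this. The wording is therapy provided, not assigned, and SC patients may later receive exploration, CRS and HIPEC, other surgery or systemic therapy. The table and the Fisher counts show that nothing is guaranteed.

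A reader might also infer that the harms of late detection go unseen. Deaths enter overall survival, recurrence and progression are compared between arms, the principal investigator reviews toxicities quarterly, and "The NCI IRB will review submitted adverse events monthly to evaluate trends", with no attribution limit stated. What these routes do not provide is a between-arm comparison of non-fatal morbidity from progression.

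Nor is there any sign of intent. The asymmetry works against the experimental arm, which some would call the cautious direction for an invasive procedure. No stopping rule is tied to this test, and nothing says that a final safety analysis inherits the filter. Finally, this is a condensed article, and the full protocol may define the safety set more exactly. That limits the weight of the point, but the article does state the filter, the comparison and the question, and together they do not fit.

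**Conclusion.** The point holds in a limited form. Read naturally, the annual between-arm toxicity comparison uses events attributed to a different reference in each arm. It is not like-for-like, it tends to overstate excess toxicity in MSLS, and it omits non-fatal, progression-related morbidity in SC.

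The size cannot be fixed from the document because it depends on the unknown share of SC events attributed. Under the stated assumptions a nominal 5% error rate becomes 50% when a quarter of SC events are attributed and 15% when half are. It vanishes if the attributed shares are equal, which the timing of treatment in the two arms makes unlikely early on. The consequence is confined to safety monitoring; the survival comparison and the sample size stand.

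**What to change.** State in Data and Safety Monitoring that the between-arm comparison for the monitoring board uses the maximal grade per patient of all serious (grade 3 or higher) adverse events from randomization, irrespective of attribution, by randomized arm, and including events after salvage treatment in SC. The Cochran-Armitage test can stay. Show attribution as a secondary breakdown, and say there whether salvage treatment counts as therapy provided on the SC arm. If the full protocol already specifies an all-cause comparison, one clarifying sentence is enough.

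The cost is a change of wording and one table, drawn from the same follow-up in both arms. The downside is more background events in both arms, which adds noise to a comparison of 35 patients each. Sample size, treatment and the primary endpoint do not change.

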### Inclusion and Exclusion Criteria

#### Inclusion Criteria

• Histologically confirmed colorectal adenocarcinoma.

• Curative resection (NED at closure) for CRC which was (1) perforated into the peritoneal cavity, (2) associated with minimal PC which was completely excised at the time of initial operation, (3) T4 lesion that required en bloc resection of additional organs, (4) associated with ovarian metastases or (5) emergency presentation with lesions associated with obstruction and/or bleeding.

◦ **Note**: Patient who presented at the time of diagnosis with limited extra abdominal metastases may be eligible if the lesions were completely resected and the patient remains NED.

• Received at least 3 months of standard of care adjuvant therapy and is disease free by conventional imaging at time of registration and randomization.

◦ **Note: **The imaging will be reviewed by an experienced radiologist and a surgical attending prior to enrollment.

• Greater than or equal to 18 years of age.

• Clinical performance status of ECOG ≤ 2.

• Stable serum CEA levels not indicating recurrence.

• No history of prior/other malignancies within the 2 years prior to enrollment with the exception of basal cell carcinoma.

#### Exclusion Criteria

• Active systemic infections, coagulation disorders, or other major medical illnesses precluding major surgery.

• Prior experimental therapy with novel agents.

• Prior HIPEC.

• History of brain metastases.

• Childs B or C cirrhosis or with evidence of severe portal hypertension by history, endoscopy, or radiologic studies or with evidence of moderate to severe ascites.

• Weight less than 40 kg.

• History of congestive heart failure and/or an LVEF < 40%.

• Significant COPD or other chronic pulmonary restrictive disease with PFT's indicating an FEV1 less than 50% or a DLCO less than 40% predicted for age.

### Intervention

#### Mandatory Second-Look Surgery (MSLS) Arm

All patients randomized to the MSLS arm will undergo exploratory laparotomy at the Surgery Branch, NCI. The overall goal for surgical therapy is to determine whether clinically occult metastases exist and to render the patient NED with negative margins if metastases are detected. All previous dissection planes should be open as feasibly and safely as possible which requires an exploratory laparotomy because most recurrences detected at sites of prior operative therapy that often have adhesions preventing laparoscopic evaluation of these areas. Determination of NED status will be based upon visual inspection, frozen biopsy of any suspicious lesions, and ultrasound of liver with biopsy as indicated. Peritoneal washings will be performed in all patients. Sixteen16 peritoneal biopsies will be done - 4 from each quadrant. Data from these investigations will be used at the final analysis of the risks and benefits of this approach. Pre- and post-operative peritoneal disease will be recorded using the PCI and the Gilly's methodology [35,36]. If any means above detect recurrent disease, all disease will be resected if technically feasible and HIPEC will be performed in all patients. Complete peritonectomy will be performed only in cases where carcinomatosis is detected and confirmed by a frozen biopsy. For patients with peritoneal disease peritonectomy and CRS includes the following: The right and left sub-diaphragmatic peritoneum, the falciform ligament, lesser and greater omentum, anterior, right and left abdominal wall down to the paracolic gutters, and the pelvic peritoneum. The surgeon has the discretion to perform partial peritonectomy for limited disease which may include one or more of the resections described above. Intra-operative hepatic ultrasound will be performed when clinically indicated.

For the HIPEC procedure, two large bore catheters (thoracostomy tubes) will be inserted through the abdominal wall incision, one over the right lobe of the liver and one in the pelvis. The abdominal skin will be closed and the catheters connected to a perfusion circuit. The perfusate passes from a reservoir through a roller pump, heat exchanger, and then into the abdominal cavity. Efflux from a second catheter is then recirculated through the reservoir and pump. The perfusion flow rate will be maintained at 2.0 L/min and a perfusate volume will be maintained which moderately distends the abdominal cavity correlating with intra abdominal pressures of 5 to 15 mm Hg (2.0 L/m^2^). Stable perfusion parameters are obtained and the peritoneal cavity is warmed to a minimum of 41°C prior to starting the clock for perfusion time and a maximum of 43°C. The perfusion will be continued for 30-35 minutes. During the perfusion, constant physical manipulation of the abdomen (shaking) will be maintained for the entire perfusion period to assure even distribution of the perfusate. The heater coil will be maintained at 46-48°C. Peritoneal temperature will be measured continuously by four probes placed immediately beneath the peritoneal surface on either side of the abdomen and in the pelvis. The patient's core temperature will be measured with an esophageal probe (which correlates well with pulmonary artery temperatures) and maintained at less than 41°C using a cooling blanket and ice packs around the legs and head. At the end of the perfusion, the abdomen will be re-opened and the perfusate irrigated from the abdominal cavity. All intraperitoneal drug dosages will be calculated on ideal body weight. 5-FU (400 mg/m^2^) and leucovorin (20 mg/m^2^) will be administered intravenously 15 minutes prior to HIPEC to potentiate the activity of oxaliplatin (460 mg/m^2 ^diluted in 2.0 L/m^2 ^of D5W via the perfusion circuit).

During the post-operative period, patients will receive all standard of care supportive measures. For patients who undergo HIPEC, these measure include when indicated: Broad-spectrum antibiotics for neutropenic fever; filgrastim for ANC less than 1000 mm^3^, and avoidance of renal toxic drugs, maintenance of good renal perfusion, and diuretics as necessary for renal dysfunction.

#### Standard of Care Surveillance (SC) Arm

Patients in both arms will undergo the same follow-up surveillance as noted in the next section. Patients who have peritoneal recurrences detected on the surveillance arm will be offered exploration if clinically appropriate with potential CRS and HIPEC pending intra-operative assessment of extent of disease.

#### Post-randomization surveillance for both arms

Follow-up will commence from randomization and will occur every 3 months for two years. After two years, follow-up will be extended to every six months, and after an additional three years, follow-up will be yearly. At any stage between these follow-ups additional evaluations will be conducted as clinically indicated. At each evaluation patients will undergo: Physical examination; laboratory tests; tumor markers; CT scan of the chest, abdomen and pelvis; PET as medically indicated. Patients on both arms who develop intra/extra-abdominal metastases will be offered standard of care surgery when indicated and/or referred to their treating physician or Medical Oncology Branch, NCI, for systemic therapy.

### Informed Consent

All patients are thoroughly screened prior to initial consultation at the NIH. During the initial consultation, the patient, along with family members, is presented a forthright and detailed overview of the treatment option available to them at the NIH. The experimental nature of the treatment, its theoretical advantages and disadvantages, and an overview of the operative procedure and anticipated convalescence are presented. The fact that the patient may undergo an operative procedure in order to receive therapy without any assurance of benefit, the aggressive nature of the treatment, and the possibility of serious or potentially life-threatening complications are presented. The Informed Consent document is given to the patient and they are asked to review it, make notes and follow-up with a phone call to the physician or nurse investigator to have any additional questions answered prior to considering treatment on protocol. The research nurse, principal investigator, or designee is responsible for obtaining consent from the patient upon admission. The signed consent will be verified by the physician responsible for the care of the patient. Patients can withdraw or decide against treatment at any time without obligation.

### Endpoints and Follow-up of Study

#### Primary Objectives

• To compare the overall survival of patients at high risk for developing PC from CRC who undergo MSLS with HIPEC and CRS (if applicable) vs. similar patients who receive standard of care surveillance.

#### Secondary Objectives

• To determine recurrence-free survival from the time of randomization in both arms.

• To investigate selection criteria for patients who might benefit from MSLS with HIPEC and CRC.

• To determine the percentage of patients who are diagnosed with recurrent peritoneal disease (gross vs. microscopic) at exploration.

• To determine the percentage of patients with recurrent disease at MSLS who are successfully debulked to R0.

• To determine the rate of clinical detection of PC during the pre-randomization period and thereby determining the denominator for this cohort of patients.

## Discussion

Colorectal cancer is the 3^rd ^most common malignancy in the United States accounting for over 100,000 new cases per year [1]. Peritoneal carcinomatosis accounts for about 13% of metastatic spread among patients who die from this disease [2]. Despite significant advances in chemotherapy with regimens such as FOLFOX and FOLFIRI, at best about 13% of patients with peritoneal carcinomatosis achieve 5-year survival with chemotherapy alone [26]. CRS and HIPEC have shown impressive results with 5-year survivals of about 50% for patients with disease limited to the peritoneum [11,13,23]. The patients who consistently experience the best survivals undergo complete resection of peritoneal disease (R0 resection). Unfortunately, this disease is not detectable by imaging, symptoms, or tumor markers early in the disease, yet early intervention is more likely to achieve complete resection of the disease. Therefore, identification of a patient population at high risk for PC may allow earlier interventionin order to undergo surgery completely resect recurrent disease has been proposed to increase survival in this patient population.

This trial tests the strategy of mandatory second-look laparotomy for patients at high risk of recurrent peritoneal carcinomatosis versus the current standard-of-care of routine surveillance. The high risk patients previously have been defined as having limited and resected peritoneal disease at initial operation, ovarian metastases, tumor perforation, T4 lesions with en bloc adjacent organ resection, and emergency presentation with bleeding and obstruction. Given that this patient population has high risk of peritoneal recurrence that translates into very poor survival, a strategy as invasive as an mandatory exploratory second-look surgery is justified to determine its impact on survival, yet this proposal should be subjected to rigorous scientific scrutiny prior to implementation outside of a clinical trial. If the primary objective of increasing overall survival is met, this trial may change the current management of patients at high risk for developing recurrent peritoneal carcinomatosis to one of aggressive, early, surgical intervention with strong evidence to show that patients will benefit from this strategy. Hopefully, this treatment will significantly increase long-term survival among patients with peritoneal carcinomatosis.

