### Statistics

The primary objective of the trial is to determine if there is a difference in overall survival among patients who are at high risk for CRC PC and are randomized to receive either SC alone or MSLS with HIPEC and CRS when indicated.

Based upon results in the literature, patients who would be eligible to be randomized on this trial and who receive SC alone would be expected to have an estimated 25% 5-year survival from the date of randomization. The goal of this study will be to determine if the use of a MSLS with HIPEC and CRS will result in patients having survival that is associated with an increase to 50% 5-year survival. Following registration, patients who are eligible for randomization will be randomized between SC and MSLS with HIPEC and CRS and followed for survival. Patients will be stratified for synchronous peritoneal carcinomatosis and ovarian metastasis vs. perforated primary and emergency with bleeding or obstruction, and prior chemotherapy ≤ 6 months vs. >6 months. Kaplan-Meier curves and a two-tailed log-rank test will be the primary analysis methods. Assuming exponential survival curves, the hazard rate for the systemic therapy is 0.0231, or approximately a 2.3% probability of dying each month when the 5-year survival probability is 25%. If we assume that the MSLS arm will have an associated survival of 50% at 5 years, this survival corresponds to a hazard rate of 0.0116, and the resulting hazard ratio for the comparison of the two overall survival curves would be 1.991. Following the principles of a phase 2.5 design, to compare these curves and detect a difference with a 0.10 one-tailed log-rank test, a total of 35 evaluable subjects per arm (70 total) will need to be randomized over a five year period, followed for an additional two years from the date of entry of the last patient, and observation of 38 total deaths in order to have 80% power to compare the curves.

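### A survival result that only just meets the one-tailed 0.10 criterion used for sizing would not by itself be the strong evidence the Discussion attaches to success

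*Protocol article*

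**What the plan says.** **Sizing (Statistics).** The calculation is introduced with "Following the principles of a phase 2.5 design, to compare these curves and detect a difference with a 0.10 one-tailed log-rank test". Surveillance patients are "expected to have an estimated 25% 5-year survival from the date of randomization", and the target for the second-look arm is "survival that is associated with an increase to 50% 5-year survival". From the rounded monthly hazards, "the resulting hazard ratio for the comparison of the two overall survival curves would be 1.991". The requirement is that "a total of 35 evaluable subjects per arm (70 total) will need to be randomized over a five year period", followed for two more years after the last entry, with "observation of 38 total deaths in order to have 80% power to compare the curves".

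**Primary analysis (same section).** "Kaplan-Meier curves and a two-tailed log-rank test will be the primary analysis methods". No significance level is given for this two-tailed test.

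**Conclusion from a positive trial (Discussion).** If the overall survival objective is met, the trial may shift management to "aggressive, early, surgical intervention with strong evidence to show that patients will benefit from this strategy". The shift in practice is worded as a possibility. The strength of the evidence is not qualified. The same paragraph asks for rigorous scrutiny before the strategy is used outside a trial. Nowhere does the article say that a positive result would be preliminary or would need confirmation.

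**The concern.** The error rate in the sizing and the conclusion in the Discussion do not match. A one-tailed 0.10 test accepts a 10% chance of declaring a benefit of second-look surgery when there is none. A conventional two-sided 0.05 test allows 2.5% in that direction, so the allowance is four times as large. With 38 deaths, a result can pass the looser criterion and leave real doubt about the direction of the effect.

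The strategy is a laparotomy in patients who show no evidence of disease on surveillance, and the article's Informed Consent section acknowledges possibly life-threatening complications. If passing the sized criterion is reported as strong evidence, such surgery could spread on a result that is statistically compatible with worse survival.

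**Working it through.** **Inputs, all from Statistics:** one-tailed alpha 0.10; power 80%; 38 deaths; hazard ratio 1.991 (0.0231/0.0116), surveillance over second look; 1:1 allocation. The calculation assumes proportional hazards, a single final analysis at 38 deaths, and the usual approximation SE(log HR) = 2/√deaths. The annual interim efficacy evaluations are not modelled.

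**1. Reproduce the plan's figure (Schoenfeld).**
Deaths = 4(z₁₋α + z_power)² / (ln HR)² = 4(1.2816 + 0.8416)² / (ln 1.991)² = 38.02. With the unrounded ratio of 2.0 the result is 37.5, which rounds up to 38. Power with 38 deaths at a ratio of 1.991 is 0.800. Two-tailed 0.10 would need 52 to 53 deaths and two-tailed 0.05 would need 66 to 67. So 38 deaths rest on the one-tailed 0.10 level.

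**2. Smallest result that passes at one-tailed 0.10.**
SE = 2/√38 = 0.324.
Critical ratio = exp(1.2816 × 0.324) = exp(0.416) = 1.52.
95% CI = exp(0.416 ± 1.96 × 0.324) = 0.80 to 2.86.
Expressed as second look over surveillance, this is 0.66 (0.35 to 1.25).

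On the survival scale, hold surveillance at the planned 25% at 5 years (an assumption for illustration). Second-look survival is then 0.25^0.66 ≈ 40%, with limits 0.25^1.25 ≈ 18% and 0.25^0.35 ≈ 62%. The lower limit is below the surveillance figure.

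**3. Result needed for the 95% interval to exclude 1.**
exp(1.96 × 0.324) = 1.89.

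**4. Chance of each result under the planned ratio of 1.991.**
Expected z = ln(1.991) × √38 / 2 = 2.12.

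| Criterion | Smallest passing ratio | 95% CI at that ratio | Power with 38 deaths |
|---|---|---|---|
| One-tailed 0.10 | 1.52 | 0.80 to 2.86 | 80% |
| Two-tailed 0.10 | 1.71 | 0.90 to 3.22 | 68% |
| Two-tailed 0.05 | 1.89 | lower limit 1.00 | 56% |

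Under the planned effect, about 0.56/0.80 = 70% of results that pass at one-tailed 0.10 would also have a 95% interval excluding 1, and about 30% would not. Under no effect, 0.025/0.10 = 25% of the passing results would have such an interval and 75% would not.

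**5. Effect of the two-tailed statement.** Read at two-tailed 0.05, a positive result excludes 1 by construction, so step 2 no longer applies. The cost appears in the last column: 56% power, not the stated 80%. Read at two-tailed 0.10, a just-positive interval still includes 1.

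**The case against.** The strongest reply has four parts.

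*The sentence is closing discussion, not a rule.* This stands. It is hedged on practice change, and the Statistics section attaches no recommendation to a positive result. A reader might infer that a practice change has been fixed in advance as the consequence of success; the document does not say so. What remains is that the strength of evidence is unqualified and follows directly from meeting the objective.

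*The design can produce strong evidence.* This also stands. A reader might infer that 38 deaths are too few for it whatever the result. Step 4 shows otherwise: under the planned effect, more than half of such trials would have a 95% interval excluding 1. The point concerns results that meet the sized criterion but fall short of a ratio of about 1.89.

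*The numbers presuppose the one-tailed level.* This is correct and limits the finding. The stated primary test is two-tailed with no level. If it is run at 0.05 the mismatch disappears and a shortfall in power replaces it. The article does not settle which applies.

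*The purpose of a phase 2.5 design is not defined in the article.* This is true, so the argument rests on the stated error rate and number of deaths. Nor can a share of false-positive results be read from the document. Assumed prior chances of 10%, 20% and 30% that the planned effect is real give about 53%, 33% and 23% (for 10%: 0.09/(0.09 + 0.08)). The finding uses none of these.

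**Conclusion.** The point holds in a limited form. If the primary objective is judged at the one-tailed 0.10 level that produces 38 deaths, meeting it is not by itself strong evidence of benefit. A just-successful ratio of about 1.52 carries a 95% interval from about 0.80 to 2.86. The evidence would exclude no effect at the 95% level only from an observed ratio of about 1.89, which has about a 56% chance under the planned effect.

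The sizing itself contains no arithmetic error. The finding depends on which test defines success, and the Statistics section leaves that open. It also assumes proportional hazards and one analysis at 38 deaths; a stopping boundary for the annual evaluations may stand in the full protocol and could alter the thresholds.

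**What to change.** 1. In Statistics, state one test, with its tails and level, that defines whether the primary objective is met, so that sizing and analysis agree.
2. If that level is one-tailed 0.10, add beside the primary analysis that significance at this level alone is preliminary evidence supporting a confirmatory trial, and that the hazard ratio will be reported with its 95% confidence interval.
3. Reword the Discussion so that the strong-evidence claim is no longer tied to merely meeting the one-tailed 0.10 criterion. One workable condition is a 95% interval that excludes 1. This threshold is a convention, but it should be named in advance.

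These are changes of wording, and the claim that a positive trial may make becomes less favourable.

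If two-tailed 0.05 is chosen instead, step 2 is not needed, but the power statement must be corrected to about 56% with 38 deaths. Restoring 80% would take 66 to 67 deaths. With the same five-year accrual and two-year follow-up, about 57% of patients are expected to die (40 of 70), so roughly 116 to 118 would have to be randomized, against the 70 to 75 planned.
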